### Study withdrawal and stopping medication

After randomization, the patients can withdraw at any time if they own wish without giving any reason.

Study treatment will be stopped for the following reasons:Any adverse event resulting from surgery that might interfere with the study drug or might lead to meaningless endpoint data (e.g., organ failure, anastomotic failure, or postoperative dementia). Due to the complexities of postoperative morbidity, no list of fixed criteria will be established. If such an event occurs before the first study medication will be taken, the patient will be withdrawn from the study and replaced by another patient.Serious adverse events occur that are definitively or probably related to the study drug.Tachycardia, defined as a pulse of over 120/min three times within 1 hour, occurs.In the investigator’s opinion, continuation of the treatment is detrimental to the patient’s well-being.

Unless the patient wishes to withdraw from the study, all scheduled examinations will be performed as planned as long as they are meaningful and do not pose an unnecessary burden to the patient (e.g., no X-ray examination will be performed if treatment is stopped very early or if the patient has multiple vomiting events during the first 3 days postoperatively). Thus, stopping the medication does not automatically constitute withdrawal from the study.

The investigator can withdraw a study patient if a reoperation before the return to normal bowel function is required, an epidural analgesia was placed, if there are signs of renal insufficiency or an acute renal insufficiency, or if the patient clearly is not compliant (repeated refusal to take study medication or is consuming caffeine-containing beverages or food).

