### Endpoints

The primary endpoint is the time to the first bowel movement. The time will be measured from the time of wound closure to the patient’s first bowel movement. Patients were advised before study participation to remember or note their first stool after surgery. A study nurse will inquire daily whether bowel movement has occurred.

The definitions of the secondary endpoints are indicated as follows. The time to tolerance of solid food is measured from the end of surgery until the patient tolerates the intake of solid food. Tolerance of food is defined as the first time the patient is able to eat solid food (any food requiring chewing) without vomiting or experiencing significant nausea within 4 h after the meal and without reversion to only enteral fluids.

Time to first flatus is the time from the end of surgery until the patient’s first flatus. The passage of flatus will be determined by questioning the patient; the passage of a bowel movement will be determined by referring to the nursing records or by the clinical judgment of the investigator or designee following questioning of the patient.

Postoperative vomiting events, determined from the nursing records, refer to the number of times the patient has to vomit.

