### Statistical analysis

One interim analysis is planned to assess the primary outcome and the safety of the treatment after 60 patients have been randomized. The statistician will provide an analysis of the primary outcome and a summary of adverse events (in particular, adverse events attributable to caffeine). In this analysis, the arm assignments will not be revealed (blinded); the arms are only labeled A, B, and C. The results will be presented to the data and safety monitoring committee (DSMC). Based on these data, the trial chairperson and the DSMC will decide whether to continue the trial without modification, continue the trial with modification, or stop the trial due to safety or efficacy concerns. If in doubt, the DSMC can ask to reveal the arm assignments before making a final decision. Early stopping of the trial for efficacy at the interim analysis should only be instituted if the benefit of the treatment is shown “beyond reasonable doubt.” A nominal p-value < 0.0007 (O’Brien Fleming alpha spending, see below) provides guidance in this instance but is not binding for this decision. No formal criteria for early stopping for safety reasons will be instituted. The DSMC will make this decision based on statistical analysis, as well as on clinical judgment.

The results of the interim analysis will be confidential and strictly limited to the trial statistician and the trial chair and co-chairs, as well as the DSMC. This confidentiality should prevent any bias by the interim results on the continuation of the trial.

Statistical analysis will be performed with a current R environment (www.r-project.org). For baseline characteristics, descriptive statistics will be used as appropriate. All confirmatory analyses will primarily be performed as an intention-to-treat-analysis, assessing all patients with available data for the outcomes according to the randomization. The significance level alpha for analysis of the primary outcome will be adjusted to the exact proportion of information included in the interim analysis if the analysis is not performed at exactly 60 enrolled patients. For all other analyses, two-sided significance tests with an alpha of 0.05 will be applied.

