To maintain the alpha level, an O’Brien Fleming alpha spending function will be used [18]. The formal significance level in the interim analysis after 60 enrolled patients is alpha = 0.0007. The alpha for the final analysis will be 0.0498 for the assessment of the time to first bowel movement in the main analysis.

For the final analysis, the superiority of caffeine over placebo for the time to first bowel movement (primary outcome) will be assessed irrespective of the caffeine dosage using a Mann-Whitney-U-statistic. Hence, the arms with 100 mg and 200 mg caffeine will be treated as one arm. To maintain the alpha level despite the interim analysis, the alpha for testing the hypothesis is 0.0498.

Secondary continuous outcomes will be assessed by regression analysis of the mean ranks considering the caffeine dosage. Colon transit time analysis will be performed while additionally stratified by gender, as colon transit time is significantly shorter in men. Categorical secondary outcomes will be assessed by logistic regression analysis considering the caffeine dosage. Final analysis will be done according to the intention-to-treat principle and compared to per-protocol analyses. Auxiliary nonconfirmatory analyses will be performed to assess the influence of baseline and treatment characteristics on the primary and secondary outcomes.

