### Sample size calculation

Sample size calculation was performed for the main outcome, the time to first bowel movement using the R environment version 3.0, and the “gsDesign” and “samplesize” packages.

In a previous study, coffee consumption reduced the time to bowel movement after surgery from 74 ± 21 h to 60 ± 21 h (mean ± standard deviation) [10]. In that study, one cup of coffee (containing 80 to 130 mg of caffeine [19]) was administered three times a day. The published results of this study were based on a mix of open and laparoscopic procedures in patients with and without epidural analgesia. Because we have access to the raw data of this study, possible bias by the type of surgical access and epidural analgesia could be eliminated. Using the raw data (per-protocol analysis), the time to first bowel movement for patients after open colon resection with epidural analgesia was 61.5 ± 18.5 h for the 21 patients receiving coffee versus 72.5 ± 19.5 h for the 25 patients receiving the placebo. The number of patients with laparoscopic surgery was too low to derive meaningful data. The standardized effect size of caffeine was estimated to be 0.5 (a reduction of 10 h with a standard deviation of 20 h). Even if the absolute time to bowel movement after laparoscopic colectomy differs from the time after open surgery, the standardized effect size for both types of access can be assumed comparable. In addition, a standardized effect size of 0.5 is usually considered to be of clinical importance for study outcomes.

Assuming a power of 80 % with a two-sided alpha of 0.05 (hypothesis: superiority of caffeine), a total of 144 patients (N = 48 in the placebo, and N = 96 in the treatment arms) are necessary to detect a standardized effect size of 0.5 for a 1:2 ratio of placebo versus caffeine (for this analysis, the two caffeine arms (100 mg/200 mg) are pooled). Assuming a 20 % dropout rate (withdrawal rate), 180 patients are required for the study. Patients who withdraw from the study before receiving the first study treatment (caffeine, placebo, or radio-opaque markers) will be replaced by other patients. Otherwise no replacement for dropout or withdrawals will be performed. A bootstrap simulation using the raw data mentioned above confirmed the parametrically determined sample size.

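### The primary analysis is called intention-to-treat but uses only available data, and one withdrawal reason applies only before bowel function returns, so exclusion can depend on the outcome

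*Protocol article*

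**What the plan says.** **Analysis set** (Statistical analysis): "All confirmatory analyses will primarily be performed as an intention-to-treat-analysis, assessing all patients with available data for the outcomes according to the randomization".

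**Endpoint** (Endpoints): "The time will be measured from the time of wound closure to the patient’s first bowel movement".

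**Test** (Statistical analysis): superiority of pooled caffeine over placebo "will be assessed irrespective of the caffeine dosage using a Mann-Whitney-U-statistic", at alpha 0.0498. No rule is given for a patient without an observed time.

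**Withdrawal** (Study withdrawal and stopping medication): "The investigator can withdraw a study patient if a reoperation before the return to normal bowel function is required, an epidural analgesia was placed". Renal insufficiency and clear non-compliance are the other reasons. Withdrawal is optional.

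**Stopping capsules** (same section) is kept apart: "Thus, stopping the medication does not automatically constitute withdrawal from the study". After stopping, "all scheduled examinations will be performed as planned as long as they are meaningful and do not pose an unnecessary burden to the patient".

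**Loss allowance** (Sample size calculation): 144 evaluable patients are inflated to 180 for 20 % dropout, which the text equates with withdrawal. Patients who leave before any study treatment are replaced. "Otherwise no replacement for dropout or withdrawals will be performed".

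**The concern.** A rank test needs a value for every patient it includes. Under the stated analysis set, a patient whose time is not observed leaves the comparison. That is an available-case analysis, whatever its label.

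This would matter little if the reasons for leaving had nothing to do with bowel recovery. One of them does: reoperation counts as a withdrawal reason only while the primary event is still outstanding. At any given rate of reoperation, a patient who recovers slowly is exposed to that rule for longer.

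Two things are at stake. If caffeine works, more of the slow patients are on placebo, and losing them shrinks the difference and the power. If caffeine does not work but slow patients are withdrawn more often in one arm, the remaining patients in that arm look faster than they should. Inflating the sample size for dropout restores precision but removes neither bias.

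**Working it through.** **1. The plan's own figures.** Inputs from Sample size calculation: difference 10 h, SD 20 h (effect size 0.5), two-sided alpha 0.05, power 80 %, ratio 1:2.

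- Placebo n = (1 + 1/2) × (1.960 + 0.842)² / 0.5² = 1.5 × 7.849 / 0.25 = 47.1, rounded up to 48 (a t-test version gives 47.7).
- Caffeine n = 96, total 144. Power with 48 and 96 is 0.807.
- 144 / 0.80 = 180.

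Both stated totals reproduce. They also show that the plan expects up to 180 − 144 = 36 patients to be absent from the primary test.

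**2. The sections side by side.**

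| Section | What it fixes |
|---|---|
| Statistical analysis | Only patients with outcome data are analysed |
| Statistical analysis | The test ranks observed times; no censoring or ranking rule |
| Study withdrawal and stopping medication | Optional withdrawal; the reoperation reason exists only before the endpoint |
| Sample size calculation | 20 % withdrawn, not replaced after first treatment |

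No section says whether a withdrawn patient's bowel movement is still recorded and used.

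**3. Simulation with a cut-off.** Assumptions: normal times, SD 20 h, means 72 h (placebo) and 62 h (caffeine), or 72 h in both arms; 60 and 120 patients; Mann-Whitney at 0.0498; a fraction q of patients with no stool at 85 h is withdrawn. The cut-off and q are not in the protocol.

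Share later than 85 h under the 10 h effect:
- placebo: P(Z > 0.65) = 25.8 %
- caffeine: P(Z > 1.15) = 12.5 %
- overall: (60 × 0.258 + 120 × 0.125) / 180 = 16.9 %

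| q, both arms | Withdrawn, of all | Mean difference | Power |
|---|---|---|---|
| 20 % | 0.169 × 0.2 = 3 % | 9.5 h | 82 % |
| 30 % | 5 % | 9.2 h | 80-81 % |
| 60 % | 10 % | 8.0-8.1 h | 71-72 % |
| 80 % | 14 % | 7.2 h | 64-65 % |

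For comparison, following everyone gives 86-87 %. Deleting 10-14 % purely at random gives 83-80 %. At q of 60-80 %, Gehan's test gives 83-85 % with withdrawn patients censored uniformly between 60 and 85 h.

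With no true effect:

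| q placebo / q caffeine | Type I error |
|---|---|
| equal (20/20 or 60/60) | about 5 % |
| 20 % / 30 % | 5.6 % |
| 20 % / 60 % | 17 %, nearly all in favour of caffeine (6 % with Gehan censoring) |

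**4. A second model without a cut-off.** A withdrawal event may strike at any time before the bowel movement, at a rate that rises by a factor e per SD of slower recovery. The placebo mean is 72.5 h.

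- True 10 h effect, same base rate in both arms, placebo exclusions of 9, 17 and 28 %: difference 9.2, 8.5 and 7.8 h; power 0.81, 0.74 and 0.65.
- No effect, exclusions of 9 % on placebo against 17 % or 28 % on caffeine: false superiority of caffeine in 7.5 % or 24 % of trials, against a nominal 2.5 % or so. With the imbalance reversed, the bias runs against caffeine.
- No effect, equal withdrawal: type I error 0.045-0.054.
- Rate unrelated to bowel time and equal in the arms: difference 10.0-10.1 h, so no bias.

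The 28 % scenarios put overall exclusions slightly above the planned 20 %; for example (60 × 0.09 + 120 × 0.28) / 180 = 22 %. They mark the upper end of the range.

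**The case against.** The strongest reply is that the text does not say that anyone's time is thrown away.

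- Bowel movements are taken from nursing records or questioning, patients are hospitalized throughout, a study nurse collects the data, and passage of stool is a discharge criterion. A withdrawn patient's time may well exist and count as available. The intention-to-treat result is also compared with per-protocol analyses, which suggests that the main set is meant to be the wider one. This stands: discarding is an inference. However, the sample size section removes the withdrawn 20 % before reaching its 144, so the plan itself counts them as absent.
- A reader might infer that patients may be withdrawn because bowel function has not returned. The protocol gives no such reason. The trigger is a required reoperation before that return. Epidural, renal insufficiency and non-compliance are not defined by slow bowels.
- A reader might also infer that tachycardia or other caffeine effects remove patients from the test. The protocol lists tachycardia, drug-related serious events and detriment to well-being as reasons to stop capsules, and says that this is not automatically withdrawal. Of the plausible caffeine-driven routes, only repeated refusal of medication is a listed withdrawal reason. Investigators and nursing staff are also blinded.
- The large losses need strong assumptions. Milder patterns leave power at about the planned 80 %, and equal withdrawal leaves type I error alone. This stands.
- Handling of missing data is often left to the analysis plan. That would answer a mere omission. Here the protocol itself fixes the analysis set, the test, the withdrawal rule and the allowance, and the difficulty comes from their combination.

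**Conclusion.** The concern holds in a limited form. Followed as written, the plan allows exclusion from the primary test to depend on the primary outcome, under an intention-to-treat label that suggests otherwise. It does not make the slowest patients drop out; that is a risk, and its size cannot be derived from the documents, which give only the overall 20 %.

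Under the cut-off model, the consequence ranges from almost none (power 80-82 %) to a serious loss (64-72 %). False-positive inflation to about 17 % requires roughly threefold withdrawal of late patients on caffeine. The second model shows the same pattern. The sample size of 144, inflated to 180, is not at fault.

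The point deserves correction because the loss is avoidable. With 12 patients randomized at the time of the article, wording can still change before the interim analysis at 60.

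**What to change.** 1. **Follow-up.** In Study withdrawal and stopping medication, state that neither investigator withdrawal nor stopping of capsules ends collection of the primary endpoint. The time of first bowel movement is recorded from nursing records or questioning until discharge for every randomized patient who received study treatment, unless the patient withdraws consent.
2. **Analysis set and test.** In Statistical analysis, replace the restriction to available data by all randomized patients who received study treatment, in the arm assigned. Right-censor times still unobserved at last observation and use the Gehan-Wilcoxon test, which reduces to the Mann-Whitney test when nobody is censored. Apply the same rule at the interim analysis.
3. **Sensitivity analysis.** Give the worst rank to patients with reoperation or death before the first bowel movement, because censoring may be informative and Gehan's test does not remove that bias by itself. Worst rank should not be primary because it changes the question. In the second model with no effect on bowel time and withdrawal unrelated to it, ranking all withdrawals worst rejected in 26 % of trials when 5 % of placebo and 19 % of caffeine patients were withdrawn.

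The first item does most of the work, since it leaves few times to censor. The cost is a protocol amendment, slightly more analysis and a less simple primary test. No extra visits are needed, and the clinical criteria for stopping treatment stay as they are.

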### Outcomes

The primary outcome of the study will be the return to normal bowel function after colon resection. The primary endpoint will be the time to the first bowel movement after surgery. Secondary objectives are the safety of the caffeine treatment, particularly the degree and perception of the known effects of caffeine, such as agitation and insomnia, and the recovery from surgery, morbidity, and mortality.

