#### Caffeine, nicotine, and sleeping habits evaluation

Before surgery, patients will be asked about their caffeine and nicotine consumption and their sleeping behavior as a reference for the following endpoints.

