#### Well-being

No classical quality-of-life instruments (such as the SF36 or EORTC QLQ-C30) will be administered because these usually cover periods of 14–28 days, which would be too long for this study. In addition, no reason exists to assume that the quality of life would differ between the treatment and placebo group, statistically or clinically. Furthermore, a reference value would be difficult to find, as the quality of life is certainly impaired before surgery. Thus, well-being with respect to the mental state will be measured for this study, which describes the current mood and state of the patient. The Basel Mental State Scale (Basler Befindlichkeits-Skala BBS), which consists of 16 bipolar items (a choice between two properties, such as tired/awake) will be used for this study. The instrument, which covers four domains (vitality, balance, extraversion, and vigilance), is well established, validated, and suitable for Swiss and German populations (the scale was developed in Switzerland) [13]. Patients will be asked to fill in the form on the afternoon of the second and fourth day after surgery (during treatment versus after treatment).

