#### Caffeine-related side effects

Patients will receive a self-administered questionnaire concerning the potential side effects of caffeine together with the well-being questionnaire mentioned above (i.e., on days 2 and 4). No established or validated instrument could be found for this purpose. Thus, the questionnaire was adopted from Liguori et al. [14] and complemented with questions regarding sleep and the patient’s self-assessment on whether the patient actually received caffeine. In addition, the established and validated Leeds sleep-evaluation questionnaire will be administered [15–17].

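### Pre-operative sleep and caffeine habits are collected as a reference, but the main models for sleep and caffeine side effects name only dose and so forgo some precision

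*Protocol article*

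**What the plan says.** All references are to the protocol article.

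- **Outcomes** makes the safety of caffeine a secondary objective, "particularly the degree and perception of the known effects of caffeine, such as agitation and insomnia".
- **Caffeine, nicotine, and sleeping habits evaluation** states that before surgery "patients will be asked about their caffeine and nicotine consumption and their sleeping behavior as a reference for the following endpoints".
- **Caffeine-related side effects** describes a self-completed side-effect questionnaire on days 2 and 4 and adds that "the established and validated Leeds sleep-evaluation questionnaire will be administered".
- **Well-being** gives the timing of the mood scale: "Patients will be asked to fill in the form on the afternoon of the second and fourth day after surgery". No pre-operative administration is mentioned.
- **Statistical analysis** sets out the secondary models: "Secondary continuous outcomes will be assessed by regression analysis of the mean ranks considering the caffeine dosage", and "Categorical secondary outcomes will be assessed by logistic regression analysis considering the caffeine dosage". One further factor is named, for one outcome: "Colon transit time analysis will be performed while additionally stratified by gender, as colon transit time is significantly shorter in men". The same paragraph closes with: "Auxiliary nonconfirmatory analyses will be performed to assess the influence of baseline and treatment characteristics on the primary and secondary outcomes".

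**The concern.** The article gives the pre-operative enquiry a purpose, to serve as a reference for later endpoints, but the main models for those endpoints do not name it. This is more than silence about a covariate list. The same paragraph adds gender to the colon transit analysis for a prognostic reason, and it assigns baseline characteristics to a nonconfirmatory tier. Read naturally, usual sleep and usual caffeine intake belong to that second tier.

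How a patient sleeps after surgery plausibly depends in part on how that patient slept before. Habitual caffeine intake may matter too, since the Study outline bars other caffeine during the trial and habitual users on placebo therefore stop; that is an inference, not something the article states. If these variables predict the answers, leaving them out of the main model keeps avoidable between-patient variation in the comparison. The intervals for insomnia and agitation are then wider than they need be, on the outcomes that are meant to show whether the drug is tolerable.

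**Working it through.** **1. The plan's own figure.** The article gives no precision or power target for sleep, side effects or well-being. Its one design calculation is for the primary endpoint: difference 10 h, SD 20 h, two-sided alpha 0.05, power 80 %, placebo to caffeine 1:2.

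n(placebo) = (1 + 1/2) × (1.960 + 0.842)² × (20/10)² = 1.5 × 7.85 × 4 = 47.1, rounded up to 48. Total 48 + 96 = 144, and 144 / (1 − 0.20) = 180. This reproduces the stated sample size exactly, but it says nothing about the secondary outcomes. Only the 144 is used below, as a scale.

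**2. What adjustment does.** In a linear model, which is an approximation when the outcome is a rank, adjusting for a baseline variable whose within-arm correlation with the outcome is r multiplies the residual variance by (1 − r²). Confidence interval width is then multiplied by √(1 − r²). With two covariates, r is their multiple correlation with the outcome. This ratio depends neither on the effect size nor on whether the caffeine arms are pooled.

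**3. Results.** The article gives no r, so r is an assumption shown over a range. The last column is 144 / (1 − r²), the number of patients an unadjusted analysis would need for the same precision.

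| r | 1 − r² | √(1 − r²) | Reduction in CI width | Equivalent unadjusted N |
|---|---|---|---|---|
| 0.1 | 0.99 | 0.995 | 0.5 % | 145.5 |
| 0.2 | 0.96 | 0.980 | 2.0 % | 150.0 |
| 0.3 | 0.91 | 0.954 | 4.6 % | 158.2 |
| 0.4 | 0.84 | 0.917 | 8.3 % | 171.4 |
| 0.5 | 0.75 | 0.866 | 13.4 % | 192.0 |
| 0.6 | 0.64 | 0.800 | 20.0 % | 225.0 |

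**4. The price.** With 144 patients and three arm means, 144 − 3 = 141 residual degrees of freedom remain. Two covariates take 2 of them, a variance cost of the order of 2/141 = 1.4 %, or about 0.7 % in width. At r = 0.1 the gain is therefore cancelled; from r = 0.3 upward the cost is small beside the gain.

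**5. Where the calculation applies.** It applies to outcomes analysed by rank regression. In a logistic model, adjustment changes the odds ratio being estimated from a marginal to a conditional one, so the table does not carry over to categorical side effects.

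**The case against.** The strongest reply is that nothing here is wrong. The article condenses a fuller document, and covariates for secondary models are commonly left to the analysis plan. Naming dosage does not exclude other terms. Calling data a reference does not promise covariate adjustment. An unadjusted main analysis with baseline factors explored alongside is a legitimate design. Much of this stands: the two sections do not contradict each other, and the dose-only analysis is valid. It does not dispose of the point, because the paragraph does allocate extra terms, gender to one main analysis and baseline characteristics to a nonconfirmatory tier. That is a stated choice, and it leaves the declared reference outside the main models.

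A second reply is that r may be low: the baseline is an enquiry about habits, not stated to use the same instrument as the outcome, and the outcomes are recorded in hospital days after a colectomy. This stands, and is why the gain is given as a range that starts near zero.

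A third is that habitual caffeine use may act differently on placebo than on caffeine, which an additive covariate would miss. That would be a matter for the supplementary analyses; under randomization an additive covariate still leaves the average comparison valid.

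Several stronger readings are tempting but not supported:

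- *The reference is never used.* The supplementary analyses of baseline characteristics extend to the secondary outcomes.
- *The safety comparison is biased.* Randomization balances good and poor sleepers in expectation.
- *The lost precision favours the drug.* Wider intervals do make a null result more likely, but the article nowhere says that a nonsignificant sleep result will be read as evidence of safety.
- *Power falls short by a known amount.* Taking an effect of 0.5 and 48 versus 96 patients, power would go from 80.7 % to 90.4 % at r = 0.5. That effect and that pooled split belong to the primary endpoint, whereas the secondary models consider dosage. For one dose against placebo (48 versus 48) at the same borrowed effect, the figures are 68.8 % and 80.7 %. No effect size for sleep or side effects is given, so neither pair describes this analysis.
- *Well-being is equally affected.* The mood scale is stated for days 2 and 4 only, so no baseline of the same measure is described.

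**Conclusion.** The point holds as a minor one about efficiency. Data declared to be a reference for the later endpoints are not named in the main models for sleep and caffeine side effects, and the article's own structure places them in the nonconfirmatory tier. The treatment comparison remains unbiased.

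What is forgone is about 5 %, 13 % or 20 % of confidence interval width if r is 0.3, 0.5 or 0.6, and 2 % or less if r is 0.2 or below. The documents do not settle which applies. The figures rest on the linear-model approximation for ranks, on an assumed r, and on outcomes analysed as continuous. The case is best for sleep and continuous side-effect scores, weaker for categorical side effects, and not made for well-being.

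**What to change.** In Statistical analysis, state that the main rank-regression models for the sleep outcomes and the continuous caffeine side-effect outcomes are adjusted for pre-operative sleeping behaviour and habitual caffeine consumption, and that the dose-only model is kept as a sensitivity analysis. For categorical side effects the same covariates may be added to the logistic models, with a note that the odds ratio is then conditional on them. Well-being need not be included.

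The cost is a sentence or two of analysis wording, one or two degrees of freedom, and a simple pre-stated rule for patients whose baseline answers are missing. No new data are needed. At the date given under Trial status 12 patients had been randomized, against an interim analysis planned at 60, and the statistician is to work with coded arms, so the choice could still be made without knowledge of the results by arm.
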